## 4.5 Study Agents

**Rifampicin** or **rifampin** (RIF) is a semi-synthetic compound derived from *Amycolatopsis rifamycinica*. It is mostly used in combination to treat TB, while other disease indications include brucellosis, leprosy, legionnaire's disease and problematic drug-resistant staphylococcal infections. RIF inhibits DNA-dependent RNA polymerase in bacterial cells by binding its beta-subunit, thus preventing transcription to RNA. Its MIC against replicating TB bacilli is 0.1 µg/ml and its minimum bactericidal activity (MBC) is 0.5 µg/mL. It is one of the rare anti-TB drugs with some activity against non-replicating cells.

The RIF molecule is quite lipophilic and hence is well and rapidly absorbed following oral administration, though high-fat meals may delay or decrease absorption. Although this phenomenon has not proven entirely consistent and reproducible, many studies have reported a negative effect of co-administered INH on the oral exposure of RIF in mice and in TB subjects [28, 36, 37]. Studies in mice indicate that INH interferes with the absorption of RIF thereby decreasing its bioavailability. In the study by McIlleron *et al.*, [37] it was observed that formulation was a contributing factor to this phenomenon, hence the lack of reproducibility across studies [38, 39].

RIF is thought to have good intracellular penetration despite its high molecular weight. The recommended daily dose is 10mg/kg up to 600mg, PO or IV, though it is unclear whether this dose was originally selected based on experimentally obtained PK/PD data. A recent study conducted in South Africa [40] demonstrates that RIF maintains a linear dose response of early bactericidal activity up to 1200mg, suggesting that the drug may be underdosed at 600mg daily. It is prepared alone or in combination and commercially available from numerous sources.

Rifampicin induces mainly cytochromes CYP3A4 and CYP2C9 and therefore reduces blood concentrations of drugs which are metabolized by these enzymes, among which anti-HIV drugs (Indinavir, Efavirenz, Nelfinavir, Saquinavir) and antifungals (Fluconazole, Itraconazole, Ketoconazole, Terbinafine).

**Isoniazid** (INH) is a first-line antituberculous medication discovered in 1952 and used in the prevention (alone) and treatment (in combination) of tuberculosis. Isoniazid is a prodrug and

must be activated by a bacterial catalase to inhibit the synthesis of mycolic acids in the mycobacterial cell wall. Consequently, INH is bactericidal to rapidly-dividing mycobacteria, with an MIC of 0.05 µg/ml and an MBC of 1 µg/ml, but is inactive if the mycobacterium is non-replicating or slow-growing.

INH is well absorbed following oral or intramuscular administration, though peak plasma concentrations are significantly affected by concomitant fatty food intake. It is recognized to have good penetration in inflamed meninges and caseous granulomas. The recommended daily dose is 5mg/kg up to 300mg, PO or IV.

INH is metabolized in the liver mostly via acetylation by the NAT-1 and NAT-2 acetyltransferases. The genetic diversity of these enzymes in humans has a marked influence on isoniazid metabolism, resulting in either toxic levels in slow acetylators or subtherapeutic levels in fast acetylators. There exist numerous polymorphisms of this gene that determine the rate of drug acetylation. Major genotypes have recently been grouped into three metabolic phenotypes: fast acetylators (FF), intermediate acetylators (FS), and slow acetylators (SS). A recent study conducted with Japanese volunteers concluded that the proper daily dose for rapid acetylators may be 1.5-times higher than that currently recommended [41]. The proportion of rapid acetylators in the Korean population has not been reported. It is estimated to be greater than 40% [42] and up to 90% [43] in the Japanese population, as opposed to the 40% figure observed among Caucasians and which was used to establish the conventional dose of 300mg daily.

**Pyrazinamide (PZA)** is a synthetic derivative of nicotinamide requiring activation by the mycobacterial enzyme pyrazinamidase, only active under acidic conditions which are thought to be found within the phagolysosomal compartment of macrophages. The conversion product, pyrazinoic acid, inhibits fatty acid synthetase I, required by the bacterium to synthesize fatty acids, though this has been disputed. It has an MIC of 6 µg/ml and is not cidal under *in vitro* conditions. Overall, its mechanism of action and reasons for good sterilizing activity *in vivo* are poorly understood. It is part of the 4-drug combination recommended by the WHO to treat drug-sensitive tuberculosis and is also included in most second-line regimens.

PZA is completely absorbed orally and only available as an oral drug, with a recommended daily dose of 20 to 25 mg/kg up to 2 grams. No significant effect of concomitant PZA has been observed on the exposure of 1st line TB drugs.

Little is known about the penetration of PZA into tissues. In a study where PZA levels were measured in tuberculous pleural effusion and psoas abscess, intralesional PZA concentrations were 5 to 10-fold lower than serum levels and below the MIC 2h post dose [44]. In contrast, PZA levels in cerebro-spinal fluid (CSF) were similar to those found in plasma, both in rabbits and in humans [45, 46].

**Kanamycin (KM)** is an aminoglycoside antibiotic belonging to the same class of drugs as Streptomycin, one of the first drugs used to treat TB in the 50's. It kills sensitive bacteria by binding to the 30S ribosomal subunit and interfering with protein synthesis. Its MIC and MBC against MTB are 2 and 6 µg/mL, respectively, with a remarkably low MBC/MIC ratio. However, KM is only used to treat serious bacterial infections due to severe renal toxicity and ototoxicity. No interaction with the metabolism of other drugs has been reported. The drug is approved by

the Korean Ministry of Food and Drug Safety (MFDS) but not the US FDA for use against pulmonary TB.

Aminoglycosides do not concentrate effectively in tissues and remain mostly extracellular, in agreement with their hydrophilic nature and low cLogP (Table 1). Accordingly, KM is not orally absorbed and is administered via the intramuscular or intravenous route at a dose of 1g daily or 750mg for subjects under 50kg of bodyweight. The epithelial lining fluid (ELF):plasma ratio of aminoglycosides used against TB ranges from <0.3 for streptomycin to <1.0 for KM. However, receptor-mediated endocytosis of aminoglycosides, by the two main receptors megalin and cubilin found at the surface of epithelial cells, plays an important role in the accumulation of aminoglycosides in renal proximal tubules [47]. Megalin has also been found on the surface of type II pneumocytes, which are critical for the establishment of mycobacterial pulmonary infections as a portal of mycobacterial organisms to the lungs.

The PK/PD parameter driving aminoglycoside efficacy is the ratio between peak concentration and MIC ( $C_{\max}/\text{MIC}$ ), with a maximum effect at  $C_{\max}/\text{MIC}$  around 10-12. Aminoglycosides have a long post-antibiotic effect, which can be described as an ability to inhibit bacterial growth well after the plasma/tissue levels have fallen below the MIC.

**Moxifloxacin (MXF)** is a synthetic fluoroquinolone antibiotic. It inhibits bacterial topoisomerase II (DNA gyrase) and topoisomerase IV, which are essential enzymes playing a crucial role in the replication and repair of bacterial DNA. Its MIC, MBC and intracellular activity against MTB are 0.5, 2 and 1  $\mu\text{g/mL}$ , respectively, with again a low MBC/MIC ratio.

Moxifloxacin is used to treat a variety of respiratory infections, as well as skin and skin structure infections. Moxifloxacin is also used for the treatment of complicated intra-abdominal infection. The usual dosage is 400 mg daily taken orally or via intravenous infusion over 1 hour. Although it is increasingly used as second line agent in MDR-TB cases, the drug is not formally approved by the MFDS or the USFDA for use against pulmonary TB.

MXF is rapidly absorbed following oral administration, reaching a mean peak drug plasma concentration within 2 h after a 400 mg dose. The rate and extent of absorption are not significantly affected by food. Moxifloxacin binds weakly to plasma proteins and penetrates well into most tissue and fluid compartments, with generally higher drug concentrations in tissues than in plasma, and good intracellular penetration [3, 48]. Of the various fluoroquinolones considered for the treatment of tuberculosis, MXF exhibits the highest ELF:plasma ratio with a value of ~6 and a 20 to 70-fold accumulation in alveolar macrophages [49].

Moxifloxacin undergoes phase II metabolism in the liver to produce sulphate and glucuronide conjugates. Induction of conjugative enzymes by RIF has not been thoroughly investigated but some effect on MXF metabolism cannot be excluded since RIF was shown to induce sulphate conjugation of one oral contraceptive [50].

**Table 1. Physico-chemical Properties of the 5 Study Drugs**

| drug       | isoniazid | kanamycin | moxifloxacin | pyrazinamide | rifampicin |
|------------|-----------|-----------|--------------|--------------|------------|
| clogP      | -0.668    | -5.173    | -0.082       | -0.206       | 3.71       |
| mol weight | 137.14    | 484.51    | 401.44       | 122.13       | 822.96     |

|                   |        |                     |                                |              |        |
|-------------------|--------|---------------------|--------------------------------|--------------|--------|
| CMR*              | 3.714  | 11.153              | 10.464                         | 3.343        | 21.925 |
| PSA (square Å)**  | 68.01  | 282.61              | 86.27                          | 55.98        | 220.15 |
| volume (cubic Å)  | 126.75 | 473.28              | 366.49                         | 113.27       | 847.56 |
| pKa               |        | 9.90/8.22/7.24/6.57 | 9.77
(amine)/3.05
(COOH) | 3.53 (amine) | na     |
| H-bond acceptors  | 4      | 15                  | 7                              | 3            | 16     |
| H-bond donors     | 3      | 15                  | 2                              | 2            | 6      |
| amide group       | 1      | 0                   | 0                              | 1            | 1      |
| rotatable bonds   | 2      | 6                   | 4                              | 1            | 5      |
| flexibility index | 14.58  | 12.38               | 9.96                           | 8.19         | 6.08   |
| logD 7.4          | -0.7   | -8.6                | -0.1                           | -0.2         | na     |
| logPm             | -2.29  | -6.55               | -4.78                          | -2.29        | -2.39  |
| water solubility  | 2      | 1                   | 2                              | 1            | 3      |

\* CMR: Computed Molar Refractivity

\*\* PSA: Polar Surface Area

#### 4.5.1 Other Agents

While on study drugs, subjects will also be receiving 2nd line agents determined by DST results as part of their ongoing regimen. The possible drugs used include but are not limited to prothionamide, para-amino salicylic acid (PAS), ofloxacin, levofloxacin, and cycloserine. There are no known interactions between these drugs and the study drugs. Subjects having received rifampin or rifabutin over the past 30 days will be excluded from the study.

## 4 Subject Enrollment

### 4.1 Accrual

Subjects with diagnosed pulmonary TB who have elected to undergo lung lobectomy will be given the opportunity to participate in the study. We expect accrual to take approximately 12 months among the three study centers of Asan Medical Center, National Medical Center, and Pusan National University Hospital.

### 4.2 Eligibility Criteria

#### 4.2.1 Inclusion Criteria

- 1) Males and Females age 20 and above
- 2) Selected for lung resection due to anti-tuberculous treatment failure, multidrug resistant disease, or other reason determined by the treating physician
- 3) Radiographic evidence of tuberculous disease of the lung(s)
- 4) If already on an aminoglycoside, ability and willingness to substitute this aminoglycoside with KM for the one study dose
- 5) Willingness to receive MRI scan and marker and Gadolinium injection
- 6) Willingness to have samples stored
- 7) Ability and willingness to give written or oral informed consent
- 8) EKG without evidence of QT\* prolongation within 1 week of study.

\* QT prolongation is considered when the QTc interval is greater than 440 ms (men) and 460 ms (women), although arrhythmias are most often associated with values of 500 ms or more.

#### 4.2.2 Exclusion Criteria

- 1) Subjects < 20 years of age
- 2) Women of childbearing potential, who are pregnant, breast feeding, or unwilling to avoid pregnancy (*i.e.*, the use of appropriate contraception including oral and subcutaneous implantable hormonal contraceptives, condoms, diaphragm, intrauterine device (IUD), or abstinence from sexual intercourse) [Note: Prospective female participants of childbearing potential must have negative pregnancy test (urine) within 48 hours prior to study entry.]
- 3) Allergy or hypersensitivity to any of the 5 study drugs or any fluoroquinolone, aminoglycoside, or rifamycin
- 4) Those with severe gout
- 5) Severe claustrophobia or Gadolinium hypersensitivity (tbc)
- 6) Renal, hepatic, auditory and/or vestibular impairment.
  - a. Serum creatinine > 2.0 mg/dL (renal )
  - b. Aspartate aminotransferase (AST or SGOT) >100 IU/L (LFTs)
  - c. Alanine aminotransferase (ALT or SGPT) >100 IU/L(LFTs)
  - d. Total bilirubin > 2.0 mg/dL(LFTs)
- 7) Documented QT prolongation
- 8) The use of any of Rifampicin (RIF), Rifapentine or Rifabutin within 30 days prior to the study
- 9) HIV infection, determined by a positive HIV test performed with the past 6 months
- 10) The use of any of the following drugs within 30 days prior to study
  - a. Systemic cancer chemotherapy
  - b. Chronic systemic corticosteroids (oral or IV only) with the following exceptions (*i.e.*, the following are NOT exclusion criteria): intranasal, topical, and inhaled corticosteroids, a short course (10 days or less) of corticosteroids for a non-chronic condition completed at least 2 weeks prior to enrollment in this study
  - c. Systemic IND agents other than linezolid
  - d. Antiretroviral medications
  - e. Growth factors
- 11) The need for ongoing therapy with warfarin, phenytoin, lithium, cholestyramine, levodopa, cimetidine, disulfiram, ergot derivatives, fosphenytoin, carbamazepine, cyclosporine, tacrolimus, sirolimus, amiodarone or phenobarbital (If a potential subject is on one of these medications but it is being stopped per standard of care, to be eligible for the study the drug must be stopped at least one day prior to receiving study drug. A longer washout period is not necessary.) The only exception to this is amiodarone; because of amiodarone's long half-life and potential for QT prolongation, it should be stopped at least 60 days prior to receiving study drugs.

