### 3 Study Design and Methods

#### 3.1 Design

This is a single-dose pharmacokinetic study of 5 concomitant drugs where resected lung tissue will be recovered to determine and compare drug levels within plasma, sputum, healthy lung and pulmonary TB lesions over a 24h period. Comparison and modeling of the concentration-time profiles in plasma and lesions are used to infer permeability coefficients, exposure ratios and concentration gradients for five major 1st and 2nd line TB drugs: RIF, INH, PZA, KM and MXF. Subjects will be randomized to receive the 5 drugs at one time point, either at 2, 4, 8, 12 or 24h prior to surgery, or as close as practical to those times with careful recording of the time of administration. Enrollment will continue until evaluable tissues from 3 subjects have been processed at each assigned time point. Blood and sputum samples will be obtained just before drug administration (trough), and blood samples will also be obtained at 2h ( $C_{max}$ ) and 6h post-dosing or as practicable. Whenever possible, one additional blood and/or sputum sample will be obtained between drug dosing and surgery. Finally, blood will be collected at the time of central line placement and sputum at the time of intubation prior to surgery. The time of each blood draw and sputum collection will be recorded as carefully and accurately as possible. Urine will be systematically collected between the time of drug administration and surgery. The removed tissue will be dissected to separate lesion material from uninvolved lung. The location of each lesion within the lung lobes will be recorded. Each lesion will be measured and weighed, then further divided to perform the following analyses: determination of overall lesional drug concentrations by liquid chromatography-mass spectrometry (LCMS), imaging mass spectrometry and histopathology analyses to visualize 2D drug distribution within lesions. A pre-operative dynamic MRI scan (30-60 min duration) will be conducted one to two weeks prior to surgery to assess lesional perfusion and endothelial function. This procedure can be performed with most MRI machines in clinical use and this may be taken at a different site. A scan will be obtained before injection of the contrast agent (gadolinium). After the contrast agent is given, the subject will be scanned serially at several time points up to 8 minutes post-injection. The rate of gadolinium uptake and its retention properties will be determined using software. The entire scan will take about 45 minutes. A subject will participate in this study from entry (1 to 2 weeks prior to surgery), through surgery and for 48h post surgery.

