### Doses:

- Rifampicin (RIF) will be dosed orally at 600mg or 450mg for subjects under 50kg of bodyweight;
- Isoniazid (INH) will be dosed orally at 300mg;
- Pyrazinamide (PZA) will be dosed orally at 1.5g;
- Moxifloxacin (MXF) will be dosed orally at 400mg;
- Kanamycin (KM) will be dosed intramuscularly at 1g or 750mg for subjects under 50kg of bodyweight

The 5 groups of subjects are distinguished by the timing of the drug administration, determined by randomization. The timing will be one of 24, 12, 8, 4, and 2 hours prior to estimated vessel and bronchus ligation time, which takes place at varying times after the start of surgery, depending on the extent of adhesions between the pleural membrane and the lung lobes. These times may vary slightly due to constraints inherent to the surgical procedure. Therefore, the exact timing of vessel and bronchus ligation relative to drug administration will be recorded accurately. Ligation marks the time of isolation between tissue compartment and plasma compartment, and will therefore be used as the time post-dosing in the PK analysis.

We will allow the following deviations from assigned timing between drug administration and vessel ligation:

- minus 1h and plus 3h for the 2h group
- minus 2h and plus 4h for the 4h group
- minus 4h and plus 6h for the 8h group
- plus or minus 6h for the 12h group
- plus or minus 12h for the 24h group

In cases where these maximum deviations are exceeded, samples will be collected and analyzed for drug content, but the data will be marked as falling outside allowable time points. To compensate for these potential fall-outs, enrollment will continue until evaluable tissues from 3 subjects falling within the allowable window are obtained in each group. Two statistical analyses will be conducted, one including only those subjects in compliance with the protocol, and one including all subjects. Both sets of results will be interpreted in light of the cause(s) for delay.

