#### **3.4.1 Study Evaluations at Entry (After Consent)**

- 1) Pregnancy test for female subjects who are of child bearing age
- 2) A clinical examination which will consist of a physical examination, including body temperature, pulse, blood pressure, respiratory rate, weight, signs and symptoms of tuberculosis
- 3) Medical history will be taken at enrollment to include any previous diagnoses of major organ systems
- 4) Sputum smear microscopy and TB culture

- 5) Medication history will include a complete history of any prescription or non-prescription medications taken, including actual or estimated start and stop dates; allergies to any medications and their formulations will be documented
- 6) A baseline Dynamic MRI scan
- 7) Sputum, urine, and blood collections for experimental tests (in Diagnostic/Laboratory Procedures)
- 8) EKG with recording of QTc interval

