### **4.7 Study Completion**

A subject will have completed the study 48 hours post surgery (vessel ligation). If a subject withdraws or is withdrawn, for any reason, before lung tissue has been transferred to the dissection team, his/her participation in the study will be completed.

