### 11.3 Incompatibilities of Study Drugs

- **RIF:** Rifampicin induces hepatic enzymes, and may increase the dosage requirements of drugs metabolized in the liver. These include corticosteroids, steroid contraceptives, oral hypoglycaemic agents, oral anticoagulants, phenytoin, cimetidine, cyclosporin and digitalis glycosides.
- **INH:** Isoniazid tends to raise plasma concentrations of phenytoin and carbamazepine by inhibiting their metabolism in the liver. The absorption of isoniazid is impaired by aluminium hydroxide.
- **PZA:** No reported drug incompatibilities.
- **KM:** Other ototoxic or nephrotoxic drugs should not be administered to subjects receiving KM. These include other aminoglycoside antibiotics, amphotericin B, cephalosporins, etacrynic acid, cyclosporin, cisplatin, furosemide and vancomycin. Streptomycin may potentiate the effect of neuromuscular blocking agents administered during anesthesia.
- **MXF:** drugs which exacerbate QT prolongation such as Solatol, a general antiarrhythmic, should be avoided.

These incompatibilities were obtained from:

Francis J. Curry National Tuberculosis Center and California Department of Health Services, 2004: Drug-Resistant Tuberculosis: A Survival Guide for Clinicians,

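### Exclusion criterion 2 accepts an oral or implanted hormonal contraceptive as the only method, while section 11.3 lists steroid contraceptives as interacting with rifampicin and makes no exception for the single study dose

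*Protocol*

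**What the plan says.** Section 4.2.2 of the protocol, exclusion criterion 2, excludes women of childbearing potential who are pregnant, breast feeding or unwilling to avoid pregnancy. It explains the last of these as "the use of appropriate contraception including oral and subcutaneous implantable hormonal contraceptives", then lists condoms, diaphragm, intrauterine device and abstinence. The list is joined by "or". No second method is asked for, and no duration after dosing is given.

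Section 11.3, in the rifampicin bullet, states: "Rifampicin induces hepatic enzymes, and may increase the dosage requirements of drugs metabolized in the liver. These include corticosteroids, steroid contraceptives". The bullet does not distinguish a single dose from continued treatment.

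Section 3.1 describes the trial: "This is a single-dose pharmacokinetic study of 5 concomitant drugs". Rifampicin is one of the five, and section 3.3 gives all five to every group.

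The moxifloxacin text in section 4.5 (Study Agents) adds that "RIF was shown to induce sulphate conjugation of one oral contraceptive".

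**The concern.** The eligibility criterion names as adequate a method that the protocol elsewhere flags as interacting with a drug every participant takes. A site applying criterion 2 as written would enrol a woman whose sole method is a pill or an implant, and the criterion would give it no reason to ask for a back-up.

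What is at stake is a possible lapse in contraceptive cover for a few days or longer after the dose, in a trial that section 10.3.1 says offers subjects no benefit. Participation ends soon after surgery, so any precaution meant to last longer has to be given before the dose. No efficacy or pharmacokinetic conclusion depends on this.

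**Working it through.** The protocol gives no figure to reproduce. The check sets the sections side by side and adds one short calculation of the time a subject remains in the study after the dose.

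**Step 1. What criterion 2 accepts.** The methods form an "or" list, and no other visible section requires a second method. That a hormonal method alone suffices is an inference from these two facts; the protocol does not say it in those words.

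**Step 2. What 11.3 says.** Steroid contraceptives are named under rifampicin, with no carve-out for one dose.

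**Step 3. Who is exposed.** All 15 planned subjects (five groups of three, section 3.3) receive rifampicin once. Exclusion 8 bars rifampicin, rifapentine and rifabutin in the 30 days before the study, so no recent rifamycin treatment should precede the study dose.

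**Step 4. What the moxifloxacin text adds.** The sentence on the oral contraceptive is there to raise a possible effect on moxifloxacin metabolism. The title of the study it cites (reference 50) describes human hepatocytes. It shows that the protocol recognises the interaction. It does not show how large the interaction is in a woman after one dose.

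**Step 5. Whether anything reconciles them.** Exclusion 11 restricts phenytoin, cimetidine and cyclosporine, which are also on the rifampicin list, and warfarin, which is an oral anticoagulant. It does not mention hormonal contraceptives. The urine pregnancy test is required within 48 hours before study entry, and section 3.4.2 repeats it before each imaging scan; the study MRI is one to two weeks before surgery. These tests come before the dose, so they do not address cover after it. No visible section asks for a back-up, or says that one dose makes it unnecessary.

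**Step 6. Time from dose to end of participation.** Section 4.7 ends participation 48 h after vessel ligation. The allowed deviations in section 3.3 include "minus 1h and plus 3h for the 2h group" and "plus or minus 12h for the 24h group".

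- Shortest: (2 − 1) + 48 = 49 h.
- Longest within the windows: (24 + 12) + 48 = 84 h.

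A subject therefore leaves the study 49 to 84 h after the rifampicin dose. Most of that span is surgery and early recovery. Any precaution lasting longer would rest on advice given beforehand.

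**Step 7. Number affected.** The documents do not say how many women of childbearing potential will enrol or what contraception they use. The number relying on a hormonal method alone may be 0 of 15.

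**The case against.** The strongest reply is that the two sections do not conflict over the period studied. Prior rifamycins are excluded for 30 days, so a hormonal method is unaffected by study rifampicin up to the dose. Only 49 to 84 h of participation follow, largely in hospital around a lung resection. Section 11.3 is a general list taken from a clinicians' guide; it says dosage requirements may rise, not that contraception becomes inadequate. Oral hypoglycaemic agents and digitalis glycosides are on the same list and are not excluded either, so the list does not work as an eligibility rule. Criterion 2 also speaks of appropriate methods and gives examples, which leaves the investigator some judgement.

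Much of this stands. A reader might infer that one dose of rifampicin makes hormonal contraception fail. The documents do not support that: they give no effect size and no offset time for a single dose. A reader might also infer that women are given no advice. That cannot be claimed, because the consent form (Appendix I) is not available and is a natural place for such advice.

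Two things survive. Hypoglycaemics and digitalis are merely not excluded, whereas criterion 2 positively names hormonal methods as acceptable. And advice in the consent form, though it could meet the safety need in practice, would not change the criterion that sites apply.

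**Conclusion.** The point holds as a minor safety inconsistency between 4.2.2 and 11.3. Criterion 2 accepts a hormonal method as the sole method, 11.3 flags that class under rifampicin without exempting a single dose, and no visible section reconciles them.

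Its size cannot be set from the documents. The effect of one dose may be small, and the number of women concerned may be zero. The conclusion rests on reading the "or" list as making one method sufficient, and on the visible text alone.

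It would be too strong to call this evidence of harm or a flaw in the trial's science. The primary endpoint, the sample size and the analysis do not depend on it. It is an optional improvement, justified by its low cost.

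**What to change.** Add to section 4.2.2, criterion 2, wording such as: a woman whose only method is an oral or implanted hormonal contraceptive must also be willing to use a condom or diaphragm, or to abstain, from the rifampicin dose for a period set by the sponsor. Thirty days is a possible value. It is an assumption, chosen to match the rifamycin window already in exclusion 8; the documents give no offset time after one dose.

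State that she is counselled before dosing about the part of the period that falls after study completion, and cross-reference the rule in the rifampicin bullet of 11.3. The women concerned can be identified from data already collected at entry, since section 3.4.1 says: "Medication history will include a complete history of any prescription or non-prescription medications taken". If the sponsor judges that one dose needs no back-up, a sentence giving the reason would resolve the inconsistency instead.

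The cost is one sentence, a counselling note and a cross-reference, with no added visit, test or sample, and the added methods are already listed in the criterion. The downside is a short extra requirement for few if any subjects. It cannot be verified after completion, and a woman unwilling to accept it would become ineligible.
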